#### Primary endpoint

The primary study endpoint is the comparative analysis of the number of detected liver metastatic lesions among Sonazoid-CEUS, conventional ultrasound and CECT in screening liver metastases. If the results show that Sonazoid-CEUS could detect more lesion than conventional ultrasound and CECT, the study will be considered to be successful because it means the data collected in the present study confirmed the diagnostic improvement provided by Sonazoid-CEUS over conventional ultrasound and CECT, Sonazoid-CEUS will be confirmed as an excellent screening tool without radiation exposure.

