#### Sample size

As sample size calculation is closely related to research design, and this study consists of several parts which involves the comparison of superiority and diagnostic accuracy, so the calculation of multiple sample sizes is carried out, followed by the larger size as the final calculation results.

For the comparison of superiority and diagnostic accuracy between conventional ultrasound and Sonazoid-CEUS, we assumed a 25–50% prevalence of liver metastatic lesions in our target population (17), while 62.5–87.7% of sensitivity, 40–60% of specificity in conventional ultrasound (12), and 73–95% of sensitivity, 65–75% of specificity in Sonazoid-CEUS according to previous literature studies (18, 19). Also, a 10% dropout rate is included, and the required number of subjects is calculated to be 330.

For the comparison of superiority and diagnostic accuracy between CECT and Sonazoid-CEUS, we also assumed a 25–50% prevalence of liver metastatic lesions in our target population, while 90% of sensitivity in CECT (19), and 73–95% of in Sonazoid-CEUS according to previous literature studies. Since no AUC has been reported, this study attempted to use AUC of 0.75, 0.85, 0.95 for sample size calculation, and a 10% dropout rate is included. The required number of subjects for this part is calculated to be 65.

The sample size was calculated on the non-parametric module of PASS software using paired non-parametric test. With all these assumptions, a minimum of 330 patients are needed to obtain 80% or 90% statistical power for non-parametric test with an α equal to 0.05, of which at least 65 cases need to have received CECT.

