### Data analysis

A commercially available software package (SAS version 9.2, SAS Analytics, Marlow, UK) will be used for all the statistical analysis, and the significance level was 0.05 for two-sided tests. Descriptive data will be mainly used in the study. Efficacy analyses of sensitivity, specificity, positive predictive value, negative predictive value and accuracy will be performed using the efficacy population including subjects who received Sonazoid-CEUS, conventional ultrasound, CECT and CEMRI in screening liver metastases.

For the comparison of superiority among Sonazoid-CEUS, conventional ultrasound and CECT, intra-individual comparison will be made in terms of the detection rate of the number of detected liver metastatic lesions with pared-samples *T*-test. And the Chi-square test or Fisher exact test will be used to compare the diagnostic accuracy of the three imaging modalities in screening liver metastases.

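### The stated power for 330 patients (65 with CECT) was derived for a non-parametric test from accuracy inputs, and does not belong to the planned primary analysis, a paired t-test on lesion numbers

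*Protocol article*

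**What the plan says.** All references are to the protocol article.

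- **Primary endpoint:** "The primary study endpoint is the comparative analysis of the number of detected liver metastatic lesions among Sonazoid-CEUS, conventional ultrasound and CECT". The study counts as successful if CEUS finds more lesions than both comparators.
- **Data analysis:** for the superiority comparison, "intra-individual comparison will be made in terms of the detection rate of the number of detected liver metastatic lesions with pared-samples" *T*-test; also "the significance level was 0.05 for two-sided tests".
- **Sample size, method:** "The sample size was calculated on the non-parametric module of PASS software using paired non-parametric test". The conclusion is "a minimum of 330 patients are needed to obtain 80% or 90% statistical power for non-parametric test with an α equal to 0.05", with at least 65 patients having CECT.
- **Sample size, inputs:** "we assumed a 25–50% prevalence of liver metastatic lesions in our target population (17"); "62.5–87.7% of sensitivity, 40–60% of specificity in conventional ultrasound (12), and 73–95% of sensitivity, 65–75% of specificity in Sonazoid-CEUS"; 10% dropout. For the CECT part, sensitivity is 90% for CECT and 73–95% for CEUS, and AUC values of 0.75, 0.85 and 0.95 were tried.

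The Sample size section presents these calculations as covering both superiority and diagnostic accuracy. It says that several sizes were worked out and the larger one kept.

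**The concern.** A power figure belongs to one test, on one variable, under one set of assumptions. Here the sizing and the primary analysis differ in both test and variable, and the assumptions are ranges.

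The change of variable matters most. Sensitivity, specificity and AUC say how often a reading is right. The power of a paired t-test on lesion numbers depends on the mean within-patient difference in count and its SD, and the document gives neither. The difference between a rank test and a t-test is secondary, since the two often have similar power.

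At stake is how the main result is read. If CEUS does not come out ahead, the protocol offers no valid basis for saying what difference the trial could have detected. If it does, the report would carry a power statement that belongs to another analysis.

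**Working it through.** **1. Can 330 be reproduced?** Inputs are the ranges above, two-sided α 0.05 and 10% dropout. For paired proportions p₁ (ultrasound) and p₂ (CEUS), with readings independent within patient:

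- discordance ψ = p₂(1−p₁) + p₁(1−p₂), difference δ = p₂−p₁
- n = (1.96√ψ + z_β√(ψ−δ²))² / δ², with total = n / prevalence / 0.9

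Examples for sensitivity at 80% power:

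| Ultrasound vs CEUS | ψ | δ | n with metastases | Total at 50% / 25% prevalence |
|---|---|---|---|---|
| 62.5% vs 95% | 0.3875 | 0.325 | 27 | 60 / 120 |
| 87.7% vs 95% (upper ends) | 0.161 | 0.073 | 235 | 523 / 1045 |
| 62.5% vs 73% (lower ends) | 0.442 | 0.105 | 313 | 696 / 1392 |
| 75.1% vs 84% (midpoints) | 0.329 | 0.089 | 324 | 720 / 1440 |

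The midpoints are (62.5+87.7)/2 and (73+95)/2. Sensitivity totals therefore run from 60 to 1440 at 80% power, and from 78 to 1925 at 90%. The same formula for specificity (divided by 1 − prevalence) gives 49 to 3276 and 65 to 4383.

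Pairing the low, middle and high values gives nine sensitivity pairs. In three of them CEUS is below ultrasound (75.1% vs 73%, 87.7% vs 73%, 87.7% vs 84%), so no superiority sample size exists there. Of 1800 variants tried (endpoint, range ends and midpoints, discordance, power, sidedness, dropout formula), 31 fall within 3% of 330. They are scattered over both accuracy measures, both powers and both sidednesses, so none can be identified as the calculation used.

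The 65 can be reached, but not uniquely. AUC 0.75 vs 0.95 with 50% prevalence, zero correlation and 80% power gives 58, and 58/0.9 = 64.4, rounded up to 65. Other combinations give 63 or 67.

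**2. How far does power vary inside the stated ranges? (proxy)** This takes one yes/no reading per metastatic patient and reads prevalence as per patient. Evaluable: 330×0.9 = 297. With metastases: 297×0.25 ≈ 74 to 297×0.50 ≈ 148. The table gives exact two-sided McNemar power to show CEUS superior, from independent to fully nested readings (nested means that every detection by the weaker method is also made by the stronger):

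| Ultrasound vs CEUS | 74 patients | 148 patients |
|---|---|---|
| 87.7% vs 73% | 0% | 0% |
| 75.1% vs 84% | 20–65% | 42–99% |
| 87.7% vs 95% | 25–46% | 53–96% |
| 62.5% vs 73% | 21–80% | 44–over 99% |
| 62.5% vs 95% | 99.9% or more | over 99.9% |

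**3. What does the planned t-test detect?** Without a mean and SD, only a standardised difference (mean/SD of the within-patient count difference) can be given. Approximately d = (1.96 + z_β)/√n. For n = 297 and 80% power, 2.80/17.23 = 0.163. From the non-central t distribution:

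| Comparison | Evaluable | d at 80% | d at 90% |
|---|---|---|---|
| CEUS vs ultrasound | 297 | 0.163 | 0.189 |
| CEUS vs CECT | 65×0.9 = 58.5, taken as 58 | 0.374 | 0.433 |

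To show how much the missing inputs matter, **assume** independent detection, no false positives and the midpoint sensitivities:

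- One lesion per metastatic patient, 25% prevalence: mean 0.25×0.089 = 0.022, SD √(0.25×0.329 − 0.022²) = 0.286, d ≈ 0.08. Power with 297 is roughly a quarter.
- An average of 3.7 lesions, 50% prevalence: mean 0.166, SD 0.797, d = 0.208. Power with 297 is about 95%.

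The lesion counts are assumptions, not protocol inputs.

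**The case against.** Several points on the other side are fair.

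- **Some combinations of the stated inputs do come close to 330.** Quoting ranges and keeping the larger size is common, and a condensed article may leave the chosen scenario to the full protocol. This stands: a reader might infer that no scenario gives 330, and the check in step 1 does not support that. It does not answer the main point, because no accuracy scenario yields power for a lesion-count difference.
- **A t-test on about 297 within-patient differences is defensible.** This stands. The document gives no lesion distribution from which to call the t-test invalid, so the point is not that a rank test must replace it.
- **The McNemar figures are neither the planned t-test nor a rank test on counts.** This stands, and they are used only to show how widely power varies.
- **Patients without metastases.** A reader might infer that they drop out of the analysis because a per-patient detection rate would be 0/0. That holds only if the Data analysis wording means a per-patient proportion. The Primary endpoint section speaks of a number of lesions. On counts of confirmed metastases, such a patient contributes a defined zero difference, which enters both mean and variance.
- **Direction.** A reader might infer that the true power must be lower than claimed. The direction is unknown.

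**Conclusion.** Wrong as written: the 80% or 90% power is attached to a test and inputs that are not those of the primary analysis. This follows from the document's own sections and does not depend on an unseen analysis plan.

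The power of the primary comparison is undetermined. The sensitivity proxy spans 0% to over 99%, with 20–99% at the midpoints. The t-test illustration spans about a quarter to about 95% at those same midpoints, depending on lesions per patient and prevalence. It is tempting to conclude that 330 is too small, but the documents do not support that: 330 may be ample or inadequate.

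These figures rest on prevalence being per patient, 10% dropout, two-sided 0.05, the stated range of agreement between readings and, for the t-test illustration, assumed lesion counts. The mismatch itself rests on none of them. It should be corrected, and the correction is cheap.

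**What to change.** 1. In Sample size, state one assumed mean within-patient difference in the number of reference-confirmed metastases and its SD (or lesions per patient with the within-patient correlation), one power and the sidedness. Do this separately for CEUS against ultrasound and CEUS against CECT, since success requires both.
2. Restate the power of the primary test with about 297 and about 58 evaluable patients. Until a mean and SD are available, give the detectable standardised differences: about 0.16 and 0.37 at 80% power, two-sided 0.05.
3. Label the present 330 and 65 as sized for diagnostic accuracy only.
4. Make Sample size and Data analysis name the same test, either the paired t-test or the Wilcoxon signed-rank test, on per-patient counts of confirmed metastases. This also settles what the detection-rate wording in Data analysis refers to.

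The cost is a recalculation and revised wording. No extra patients are required by this change, and the restated power may move in either direction.

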### C (comparison or control)

Kupffer phase whole liver scan for metastases (KPWLSM) is a self-control, blind map-reading, single-center, prospective superiority trial. We set Sonazoid-CEUS, and CECT as the test group, and conventional ultrasound as the control group.

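### Primary success needs wins over both conventional ultrasound and CECT, but the quoted 80% or 90% power comes from two separately sized comparisons, so power for the success rule is lower

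*Protocol article*

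**What the plan says.** The Primary endpoint section gives the success rule: "If the results show that Sonazoid-CEUS could detect more lesion than conventional ultrasound and CECT, the study will be considered to be successful". The natural reading is that both comparators must be beaten.

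The Sample size section treats the two comparisons one at a time and explains that "the calculation of multiple sample sizes is carried out, followed by the larger size as the final calculation results". For conventional ultrasound, "a 10% dropout rate is included, and the required number of subjects is calculated to be 330". For CECT, "The required number of subjects for this part is calculated to be 65", also with 10% dropout. It then closes with one statement for the combined design: "a minimum of 330 patients are needed to obtain 80% or 90% statistical power" "for non-parametric test with an α equal to 0.05", at least 65 of these patients having had CECT. The inclusion criteria make CECT optional beyond that minimum. The Data analysis section adds that "the significance level was 0.05 for two-sided tests".

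The comparison item of the PICOT summary assigns the roles differently: "We set Sonazoid-CEUS, and CECT as the test group, and conventional ultrasound as the control group".

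**The concern.** Power of 80% or 90% for one test is not power of 80% or 90% for a rule that needs two tests to succeed. Each comparison is sized alone, and no section gives the power to win both. Keeping the larger sample size would cover both comparisons only if every patient contributed to both. Here only 65 patients are assured for CECT, so the other 265 (330 − 65) add nothing guaranteed to that comparison.

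A reader who sets the single power statement beside the single success rule will expect the primary rule to be met with 80% or 90% probability if the assumptions hold. The actual probability is lower, and the article gives no figure for it. The power statement also leaves open whether 80% or 90% applies, and to which comparison, so a reader cannot work out the joint figure alone.

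**Working it through.** **Inputs.** From Sample size: 330 and 65 patients, power 80% or 90%, α 0.05, 10% dropout. From Data analysis: two-sided tests. From Primary endpoint: both comparisons must be won. The correlation between the two test statistics is not given, so it is an assumption with a range.

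**The plan's own figures.** 330 and 65 cannot be uniquely reproduced, because the inputs are ranges and neither the paired discordance nor the AUC correlation is stated. Some combinations come close:

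- Paired sensitivity 62.5% against 73%, 80% power, two-sided, minimum discordance: 73 diseased patients. At 25% prevalence, 73/0.25 = 292. With dropout, 292/0.9 gives 325, or 292 × 1.1 gives 322.
- Paired AUC 0.75 against 0.95, 80% power, two-sided, prevalence 50%, correlation 0: 58 patients, and 58/0.9 gives 65.

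Other admissible combinations run from under 100 to over 1,000. The point does not depend on this, because the stated power is taken at face value for each comparison.

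**Range for the correlation.** Suppose the ultrasound comparison averages a within-patient difference over 330 patients and the CECT comparison averages another over 65 of the same patients. If the two differences have within-patient correlation r, the test statistics have correlation

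ρ = r × √(65/330) = 0.444 r.

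So r = 0.5 gives ρ = 0.22, and r = 1 gives the ceiling of 0.44. An equal 10% loss from both numbers leaves the ratio unchanged. The lower end is taken as 0, because the Sonazoid-CEUS count enters both differences with the same sign.

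**Joint power.** If the comparisons have power p₁ and p₂, the power to win both is Φ₂(z(p₁), z(p₂); ρ), the bivariate normal distribution function, with z(0.8) = 0.842 and z(0.9) = 1.282. At ρ = 0 it is p₁ × p₂.

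| Power per comparison | ρ = 0 | ρ = 0.22 | ρ = 0.44 |
|---|---|---|---|
| 80% and 80% | 0.640 | 0.659 | 0.680 |
| 80% and 90% | 0.720 | 0.732 | 0.747 |
| 90% and 90% | 0.810 | 0.818 | 0.829 |

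**What the quoted power would cost for the rule itself.** Under independence, 80% joint power needs √0.80 = 89.4% per comparison. Relative to 80% each, the sample size ratio is ((1.960 + 1.250)/(1.960 + 0.842))² = 1.31, which takes 330 to about 434 and 65 to about 86. For 90% joint power, each comparison needs √0.90 = 94.9%. The ratio relative to 90% each is 1.23, giving about 406 and 80.

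**The case against.** **The power statement refers to a test.** The sentence continues "for non-parametric test with an α equal to 0.05", and nowhere does the article call the figure the probability of success. This stands: no calculation in the article is shown to be wrong. The gap is between the power that is quoted and the rule that decides the primary endpoint.

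**The shortfall depends on an unstated choice.** If both comparisons were sized at 90%, joint power is 81–83%, still above the lower quoted figure. This also stands, and is why the result is given in three cases.

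**65 is a floor.** More CECT patients would help. If 65 give 80% power, 100 would give Φ(2.802 × √(100/65) − 1.960) = Φ(1.515), about 94%, and joint power with an 80% ultrasound comparison would be about 0.80 × 0.94 = 75% under independence. But no more than 65 are assured.

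**Stronger readings that the documents do not support:**

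- A reader might infer that the CECT comparison has almost no power, since most of the 73–95% sensitivity assumed for Sonazoid-CEUS lies below the 90% assumed for CECT. But the primary endpoint is the number of lesions detected, compared by a paired t-test, and the article describes AUC values as used for the CECT sizing. A patient-level sensitivity test is neither.
- A reader might take joint power as the chance that the study as a whole is declared successful. The Secondary endpoint section has its own success statement, so the figures here apply only to the primary rule.
- A reader might infer from the PICOT comparison item that Sonazoid-CEUS against CECT lies outside the planned comparisons. The outcome item and the Primary endpoint, Secondary endpoint, Sample size and Data analysis sections all include it. What remains is an inconsistent label.
- Quoting the full mathematical range from perfect negative to perfect positive correlation would overstate the uncertainty, since nesting 65 in 330 rules out both extremes.

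**Conclusion.** The point holds as one about power only. With the stated power taken as per comparison and ρ between 0 and 0.44, the chance of meeting the primary rule is about 64–68% (80% each), 72–75% (80% and 90%) or 81–83% (90% each). In every case it is below the power of the weaker comparison. Which case applies cannot be determined from the article.

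The result rests on reading the rule as requiring both wins, on each win meaning significance at two-sided 0.05 (which the Primary endpoint section does not say), on exactly 65 patients with CECT, and on approximately normal test statistics. It is worth correcting, but it does not invalidate the design.

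**What to change.** In Sample size, say which power applies to which comparison, label it as per-comparison power, and add the lower joint power for the primary rule with its correlation assumption. In Primary endpoint, state that both comparisons must be significant at two-sided 0.05 and that no alpha adjustment is therefore needed. In the PICOT comparison item, name Sonazoid-CEUS as the test and both conventional ultrasound and CECT as comparators, so that it agrees with the primary endpoint.

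The cost is a few sentences and a less favourable figure, with no extra patients. Only if the sponsor wants the quoted power to apply to the rule itself would both the total and the CECT subset have to grow, by roughly the ratios shown above.

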#### Data management

For timely desensitization of personal information, once a patient has enrolled in research, he/she will get the number immediately which will become the unique identification without the appearance of their real name again during the whole clinical projects. Trained researcher will document in writing and submit the CRF to the expert committee for data checks in the accuracy and completeness. We will record detailed patient information, primary site status, treatment process, and response to anti-angiogenic therapy and immunotherapy. Relevant follow-up data will be collected with telephone interviews 3 and 30 days after KPWLSM. Using an electronic CRF, the collected data will be entered into the database for specialized storage. After all participants finishing the project, the dataset will be reviewed and analyzed accordingly.

### Data analysis

A commercially available software package (SAS version 9.2, SAS Analytics, Marlow, UK) will be used for all the statistical analysis, and the significance level was 0.05 for two-sided tests. Descriptive data will be mainly used in the study. Efficacy analyses of sensitivity, specificity, positive predictive value, negative predictive value and accuracy will be performed using the efficacy population including subjects who received Sonazoid-CEUS, conventional ultrasound, CECT and CEMRI in screening liver metastases.

For the comparison of superiority among Sonazoid-CEUS, conventional ultrasound and CECT, intra-individual comparison will be made in terms of the detection rate of the number of detected liver metastatic lesions with pared-samples *T*-test. And the Chi-square test or Fisher exact test will be used to compare the diagnostic accuracy of the three imaging modalities in screening liver metastases.

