### I (intervention)

All patients will receive the examinations of Sonazoid-CEUS, conventional ultrasound and contrast-enhanced MRI (CEMRI), and 65 of them should have additional CECT scans.

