### Study participants

#### Inclusion criteria

Inclusion criteria (must meet ①, ②, ③ and ④)

① The history of malignant tumors prone to liver metastasis (with or without specific liver metastasis, mainly non-epigastric malignancies);

② have done or plan to have a CEMRI examination within 2 months;

③ Age 18–75 y;

④ have done or plan to have a CECT examination within 2 months (optional, but at least 65 patients should finish it).

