### Schedule of the study

After obtaining informed consent, the study group will check both of the inclusion and exclusion criteria, participants' background and pregnancy status. Four training cases and 330 formal cases were included consecutively, and all subjects will be subjected to conventional ultrasound, Sonazoid-CEUS, CEMRI examinations, 65 of which should also be subjected to CECT examinations.

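### Read literally, the efficacy population requires CECT, so the Sonazoid-CEUS versus conventional ultrasound accuracy comparison could rest on as few as about 65 of 330 patients

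*Protocol article*

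**What the plan says.** The Data analysis section of the protocol article states: "Efficacy analyses of sensitivity, specificity, positive predictive value, negative predictive value and accuracy will be performed", and continues "using the efficacy population including subjects who received Sonazoid-CEUS, conventional ultrasound, CECT and CEMRI in screening liver metastases". It names one population, with the four examinations joined by a plain conjunction. No other analysis population is given for these measures.

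The design does not give all four examinations to everyone. Under the intervention heading: "All patients will receive the examinations of Sonazoid-CEUS, conventional ultrasound and contrast-enhanced MRI (CEMRI), and 65 of them should have additional CECT scans". Schedule of the study repeats this: "65 of which should also be subjected to CECT examinations". Under Inclusion criteria, CECT is "optional, but at least 65 patients should finish it".

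The Sample size section makes two separate calculations. The first is introduced with "For the comparison of superiority and diagnostic accuracy between conventional ultrasound and Sonazoid-CEUS", takes sensitivity and specificity as inputs, and ends with "a 10% dropout rate is included, and the required number of subjects is calculated to be 330". The second, for Sonazoid-CEUS against CECT, ends with "The required number of subjects for this part is calculated to be 65".

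The next paragraph of Data analysis compares lesion counts within patients by a paired t-test (the primary endpoint). It names no population.

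**The concern.** The patients without CECT have everything needed to compare Sonazoid-CEUS with conventional ultrasound: both ultrasound examinations and the CEMRI that feeds the reference diagnosis. A population that also requires CECT leaves them out of that comparison for no reason connected with it.

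Two things are at stake. The first is precision: the accuracy part of a comparison planned on 330 patients could be analysed in about a fifth of them. The second is representativeness. CECT may have been done already or be planned, at the patient's or clinician's option, and no random selection is described, so accuracy in that subset may differ from accuracy in the consecutive cohort. If the wording stays ambiguous, the choice between the two analysis sets could also be made after the results are known.

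**Working it through.** **Inputs (protocol article).** 330 enrolled; CECT in at least 65; 10% dropout; prevalence 25–50%; conventional ultrasound sensitivity 62.5–87.7% and specificity 40–60%; Sonazoid-CEUS sensitivity 73–95% and specificity 65–75%; power 80% or 90% (all Sample size); two-sided 0.05 (Data analysis).

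**The plan's own figures.** The dropout step is consistent: 297 / 0.90 = 330, and 58 / 0.90 = 64.4, rounded up to 65. The 330 itself cannot be uniquely reproduced. The inputs are ranges, two powers are named and no within-pair correlation is given; the methods tried gave totals from about 50 to over 4,000. The point rests on the counts 330 and 65, not on that formula.

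**Patients lost.** At the floor, 330 − 65 = 265, or 265 / 330 = 80%. Because 65 is a minimum, the loss shrinks if more patients have CECT:

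| Patients with CECT (65 is the plan's floor; the rest are illustrative) | Left out | Interval width relative to 330, √(330/n) |
|---|---|---|
| 65 | 265 | 2.25 |
| 100 | 230 | 1.82 |
| 150 | 180 | 1.48 |
| 200 | 130 | 1.28 |

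**Power without choosing an effect size.** By the normal approximation, a test with 80% power at 330 has expected z = 1.960 + 0.842 = 2.802. At 65 this becomes 2.802 × √(65/330) = 1.243, and power is Φ(1.243 − 1.960) = 24%. Starting from 90%, z = 3.242 becomes 1.439 and power is 30%.

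**Power at the midpoints of the plan's ranges.** These figures assume an exact two-sided McNemar test, which the plan does not name, and 50% prevalence. Midpoints are 75.1% vs 84% for sensitivity and 50% vs 70% for specificity. Patients per disease class: 297 / 2 ≈ 148 in the full cohort, and 58 / 2 = 29 in the CECT subset if the 10% dropout applies to it. If all 65 complete CECT, it is about 32.

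The correlation between the two readings is not given, so the range runs from independent to fully nested readings (conventional ultrasound never right where Sonazoid-CEUS is wrong). The discordant proportions, Sonazoid-CEUS right only / conventional ultrasound right only, are:

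- Sensitivity, independent: 0.84 × 0.249 = 0.209 / 0.751 × 0.16 = 0.120. Nested: 0.089 / 0.
- Specificity, independent: 0.70 × 0.50 = 0.35 / 0.50 × 0.30 = 0.15. Nested: 0.20 / 0.

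Power is the sum, over the binomial number of discordant pairs, of the probability that the exact sign test rejects. The halfway case halves the smaller proportion and keeps the difference.

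| Measure | n per class | Independent | Halfway | Nested |
|---|---|---|---|---|
| Sensitivity | 148 | 42% | 60% | 99% |
| Sensitivity | 32 | 8% | 9% | 6% |
| Sensitivity | 29 | 7% | 7% | 4% |
| Specificity | 148 | 93% | 99% | 100% |
| Specificity | 32 | 28% | 38% | 64% |
| Specificity | 29 | 25% | 33% | 54% |

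At 25% prevalence the number of metastatic patients is 74 of 297 or 14 of 58. Sensitivity power then falls from 20–65% to under 2%.

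**The case against.** The strongest reply is that the sentence says the population includes patients with these examinations, not that it is limited to them, and may simply be listing the study's modalities. The Sample size section is already pairwise, with 330 for one comparison and 65 for the other, so pairwise populations may be what the authors intended. That is plausible. But no section states it, the wording literally names all four examinations, and a fuller document that used pairwise sets would depart from what is published here. This is a stated rule that conflicts with the design, not detail left out of a condensed article.

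Four limits stand:

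- A reader might infer that the whole 330-patient comparison, primary endpoint included, is confined to the CECT subset. The text does not support that. The population is attached to the accuracy measures; the paired lesion-count test has none stated, and a within-patient comparison of two modalities needs only those two.
- The 65 is a floor, so the 80% loss and 2.25-fold widening are worst cases. The 58 is lower still: if 65 patients do finish CECT, as the inclusion criterion asks, no further 10% should come off.
- The sensitivity power of 4–7% is the bleakest measure, and part of it reflects the assumed effect: even with 148 metastatic patients and independent readings, power is only 42%. Specificity fares better, but its power still falls steeply.
- A reader might infer that the CECT patients are known to be unrepresentative. Nothing in the article shows how they differ; optional selection makes bias possible, not established.

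**Conclusion.** The point holds for the accuracy analyses. The efficacy population as worded conflicts with a design in which CECT is optional, and followed literally it could leave the Sonazoid-CEUS versus conventional ultrasound accuracy comparison with as few as about 65 of 330 patients. At that floor, intervals are about 2.25 times wider and 80–90% power becomes about 24–30%. At the range midpoints, with 50% prevalence, assumed exact McNemar tests and 29 rather than 148 patients per class, power falls from 42–99% to 4–7% for sensitivity and from 93–100% to 25–54% for specificity. The exact size depends on how many patients have CECT and on the unstated correlation between readings; the direction does not. The primary lesion-count test is left undefined rather than wrongly restricted. The wording should be settled before analysis.

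**What to change.** In Data analysis, replace the single efficacy population with two:

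- **Population A:** all patients with conventional ultrasound, Sonazoid-CEUS and the reference diagnosis. Use it for Sonazoid-CEUS versus conventional ultrasound (330 planned, about 297 after 10% dropout). CECT is not an entry condition.
- **Population B:** patients in A who also had CECT. Use it only for comparisons involving CECT (at least 65 planned, about 58 if the 10% dropout applies to them).

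State that the paired lesion-count comparison uses the same pairwise populations. It would also help to tabulate the baseline characteristics of B against the rest of A, so that readers can judge whether the CECT subset resembles the cohort. The cost is a few sentences and one descriptive table; no new patients or examinations are needed.
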